#### 2.1.4. *Implementation.*

The signals and scores are transmitted between recording and processing applications using the Lab Streaming Layer protocol (LSL, San Diego, USA, v1.16.0, Stenner et al., 2022 [56]).

**Acquisition and real-time preprocessing**. All the real-time pre-processing steps and their implementation are presented in Fig 3. Our platform is using the OpenViBE software (Renard et al., 2010 [57], modified version 3.6.0-NIRS, accessible on the git repository of the platform) to perform the acquisition for the EEG and the real-time pre-processing steps for both EEG and fNIRS signals and real-time pre-processing. The EEG is acquired using the OpenViBE Acquisition server software which implements drivers for the Brain Products ActiCHamp amplifier (OpenViBE configuration: 25 samples sent per block of signal). The EEG data is sampled at 500 Hz with Fpz as the ground electrode. For fNIRS signal acquisition, the NIRStar software is used (v15.3, NIRx, Berlin, Germany) to send the raw signal to the OpenViBE acquisition server software through LSL (OpenViBE configuration: 1 sample sent per block of signal). The fNIRS signal is sampled at 6.25 Hz with 10 sequential steps of LED sources lighting (1: S1, 2: S2, S13; 3: S3, 4: S4, S15; 5: S5, S12; 6: S6, S9; 7: S7, S11; 8: S8, S10; 9: S14; 10: S16). Once entered into the OpenViBE Designer software, the fNIRS and EEG signals undergo several processing steps as described in the previous section. For the fNIRS preprocessing steps, we adapted to real-time processing the MNE functions (MNE-Python, Gramfort et al., 2013; MNE-NIRS, Luke et al., 2021 [58,59]) that perform the conversion to optical density (mne.preprocessing.nirs.optical_density), the conversion to hemoglobin states (mne.preprocessing.nirs.beer_lambert_law) and the short channels correction (mne_nirs.signal_enhancement.short_channel_regression). The localization of the long and short channels (i.e., x, y, z coordinates, obtained from the “probe-info.mat” file generated by NIRStar) is extracted to identify the nearest short-channel to each long-channel.

**Neurofeedback score metaphor.** The implementation of the score metaphor is presented on Fig 4. We chose a visual feedback adapted from the work of Perronnet et al. (2020) [28]. The NF paradigm includes the use of a visual metaphor consisting of a vertical gauge with a yellow ball moving up and down in 1D. The ball position represents the EEG scores, fNIRS scores or the average of both EEG and fNIRS scores. The background of the 1D gauge is divided into four regions to provide the subject with reference points. The NF score calculation is carried out using a dedicated Python code (Python 3.12). Visual instructions and feedback are presented to the user using the PsychoPy toolbox (Peirce et al., 2019, version 2023.2.3 [60]). The ball position ranges from 0% to 100%. If the NF score exceeds 100%, it is capped at 100%, and if it is negative, it is set to 0%. Both the *NF*_*EEG*_ and *NF*_*fNIRS*_ score is transmitted to the Python Psychopy script through LSL and the ball position is updated accordingly. Every time a new score arrives, the ball position is updated.

**Fig 4 pone.0331177.g004:**
[figure not shown]
Implementation of NF score computing and visual representation. *The calibration score*
${dif\;\;\;f\Delta HbO}_{2}$ obtained during the calibration session. With the epoching, a new score is computed every 0.25 s for the EEG and every 0.48 s for the fNIRS.

**Final set-up.** The experimental setup is illustrated in Fig 5. The cables of the EEG and fNIRS system could be lifted using a mechanical support arm (Fiber Arm, NIRx) to reduce the weight on the head and minimize the possibility of cap movement. Technical tests showed that the platform works as expected: it simultaneously records the fNIRS and EEG signals, calculates the NF scores and updates the visual feedback accordingly. The synchronization of these several steps is presented on Fig 6.

**Fig 5 pone.0331177.g005:**
[figure not shown]
Final set-up EEG-fNIRS-NF experimental platform. **A.** Schematic representation of the installation of a participant in a dedicated dark room (to avoid light noise). The fNIRS (NIRScout XP, NIRx) and EEG (Actichamp, BrainProducts) systems are connected to the experimenter’s computer to launch acquisition and signal feedback. **B.** Picture of a pilot participant with the complete cap set-up with the cables lifted by the fiber support arm.

**Fig 6 pone.0331177.g006:**
[figure not shown]
Synchronization of the several steps on the EEG-fNIRS-NF experimental platform. **A.** EEG and fNIRS raw signals acquisition. Alternance of 15 s rest (R) and 15 s NF-trial (T) periods. **B.** NF_EEG_ and NF_fNIRS_ scores calculation for all of the 10 NF-trials **(T)**.

### 2.2. Study protocol

We present now the study protocol we propose to assess the benefit of multimodal EEG-fNIRS-NF with the platform previously presented. This study was approved by the National Ethics committee of Inria (COERLE, Inria Operational Committee for the Assessment of Legal and Ethical Risk, nº 2024−27). The data acquisition started 1st of December 2024 and is running until 30th June 2025. Results of the acquisition are expected by September 2025.

#### 2.2.1. *Participants.*

Thirty healthy adults will be recruited. The inclusion criteria are i) 18-year-old or older, and ii) right-handed (score > 0.5 Edinburgh inventory, Oldfield, 1971 [61]). The non-inclusion criteria are i) to report a neurologic or psychiatric disease, ii) to report left upper limb (UL) orthopedic issues. All participants will have to read an information letter and sign an informed consent form before participating in the experiment.

#### 2.2.2. *Study design.*

This is an interventional randomized controlled study. All participants will undergo a single 90 minutes session with 45 minutes of installation and questionnaires and 45 minutes of experiment (with ~32.5 min of NF and MI task). The experiment will take place in a quiet isolated room. The participants will be equipped with our fNIRS-EEG neuroimaging system (see detailed description in section *2.1.*1. Cap-layout**) and then will perform a MI task with a visual NF in three experimental conditions repeated two times: fNIRS-based NF, EEG-based NF and EEG-fNIRS-based NF. The order of the three conditions will be randomized with control for age and gender. Participants will be blinded to the neuroimaging condition as both EEG and fNIRS systems will be set up and record brain activity during the whole session. **Fig 7** shows a flow diagram of the study design.

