**Instructions and task.** Participants will be instructed that, during the NF runs, they will see a ball moving along a one-dimensional vertical gauge. They will be asked to raise and maintain the ball as high as possible by imagining movements of their left hand. To encourage self-learning, only implicit instructions will be provided, allowing participants to explore and develop their own strategies [62]. These instructions will be displayed in written form on the screen at the beginning of each NF run (instructions available on the git repository). More specifically, participants will be instructed to perform both kinesthetic and visual MI of their left hand to control the ball [63]. Engaging the non-dominant hand in right-handed individuals may require more focused attention, thereby increasing cognitive load and promoting neural plasticity [64]. Kinesthetic MI involves attempting to feel the motion while visual MI involves imagining the movement as vividly as possible [65]. The experimental protocol will consist of two phases. First, participants will complete a preliminary MI run without NF (MI-pre) to calibrate the NF scores. Second, they will perform two NF runs for each of the three conditions: EEG-based, fNIRS-based, and EEG-fNIRS-based NF. A one-minute break will be given between the two runs and a five-minute break will be provided between conditions. During the five-minute break, participants will fill out a questionnaire on the experimental computer. Each of the six NF runs will follow a block design alternating between ten 15 s rest periods and ten 15 s task periods, resulting in a 5 minutes run. The calibration session will alternate between five blocks, resulting in a 2.5 minutes lasting run. During rest periods, the screen will display a white cross and participants will be asked to focus on the cross and disengage from the MI task, allowing their thoughts to drift (see Fig 8).

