**Fig 8 pone.0331177.g008:**
[figure not shown]
The experimental protocol will begin with a preliminary motor imagery run without NF for calibration, consisting of five alternating 15-second rest and task periods (MI task of the left upper limb). This will be followed by three conditions: two EEG-fNIRS runs, two EEG-based NF runs and two fNIRS-based runs, in randomized order across the participants. Each run will follow a block design, consisting of ten alternating 15-second rest and task periods. The NF score will be calculated based on the brain activity over the right primary motor cortex), corresponding to C4-EEG electrode and D1-S1/D2-S2 FNIRS channels in our layout.

**Neurofeedback evaluation.** In accordance with the CRED-nf checklist [66], the subjective feeling of success and the mental strategies used to control the ball movement will be gathered during an interview after the two runs of each NF condition. Participants will have to fill out a custom-made form asking: i) the type of movement imagined during the runs; ii) the strategy used for the task (open question); iii) the level of the MI kinesthetic and visual information; iv) the level of sleepiness; v) the feeling of controlling the NF; and vi) the feeling of ability to disengage from the MI task at rest.

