**Mental strategies for neurofeedback.** After each of the three NF conditions, participants will complete a questionnaire about the strategies they used during the task. Questions will be: “What type of movement did you imagine to move the ball?” and “Describe the strategy you used to perform the task” (e.g., ball fixation, focus, self-encouragement, visualization, etc.). Additionally, participants will rate their feelings of control over the gauge and their ability to disengage from the MI-NF task using a visual analogue scale (VAS). They will be asked: “Did you feel like you were in control of the gauge?” and “Did you feel it was easy to disengage from the task?” The VAS consists of a straight line, where 0 represents “not at all” and 10 represents “totally”.

**Neurofeedback scores.** All fNIRS-based and EEG-based NF scores (*NF*_*fNIRS*_, *NF*_*EEG*_ and *NF*_*fNIRS-EEG*_) will be stored and organized according to the condition (EEG, fNIRS, EEG-fNIRS) and the run [1,2]. Within each run, all scores will be averaged to produce a global NF score per condition and per run. Moreover, the time course of the scores will be extracted. The process for calculating these scores is outlined in the section Neurofeedback score.

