#### 2.2.5. *Statistical analysis.*

Statistical analysis will be performed using the latest version of the R software. A significance level of p < 0.05 will be used for all analyses. The primary outcome will be the difference in the brain activity between the three conditions: EEG-based NF, fNIRS-based NF and EEG-fNIRS-based NF. To check that the participant has succeeded, at least to some extent, in performing the neurofeedback task in each condition, we will study the NF scores. The exploratory outcomes will include the perception of control over the gauge and the strategies employed in relation to the NF condition as well as the link between the MI abilities and the performance at the NF-task. To assess the normality of the NF scores and brain activity data (i.e., EEG-ERD, EEG-ERS, fNIRS-HbR, fNIRS-HbO_2_), the Shapiro-Wilk test will be conducted. If the data are normally distributed, parametric repeated measures ANOVA will be used for mean comparisons. In cases where the data do not follow a normal distribution, non-parametric Friedman tests will be employed to evaluate differences among conditions. The perception of control over the gauge, as a function of the NF condition, will also be compared using the Friedman test. Lastly, as an exploratory analysis, Pearson correlation coefficient will be used to examine the relationship between the feeling of NF control, the MI abilities and the NF scores, depending on the NF condition.

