Finally, the design of the NF protocols plays a critical role in shaping the underlying neural mechanisms that support learning and plasticity. NF is thought to promote plastic changes through repeated, reinforced activation of specific brain circuits, consistent with principles of operant conditioning and Hebbian learning [3,88]. In our study protocol, we chose a block design in order to facilitate stronger and more consistent activation of targeted neural networks over time, promoting experience-dependent synaptic modification and functional reorganization [2]. This block design, coupled with real-time feedback and repeated training, creates the conditions for neural adaptation and learning, even if the exact causal pathways remain an active area of investigation [3].

The designed protocol aims to achieve an increased brain activity in the right primary motor cortex, the participants being instructed to mentally simulate left hand movement. Nevertheless, as the strategy used will only be subjectively reported, we will not be able to really track if the strategy might change from block to block and the subjective report will not necessarily refer to the whole condition. The reporting strategies will nevertheless give us a general idea of the most successful strategy used, and via the quality of the MI (using KVIQ scale, [67]), we will be able to see if participants feel they have mastered mental movement simulation.

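### No period term is named for the three-condition crossover, and order is controlled only for age and gender, so any trend over the session becomes error and costs precision (not bias)

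*Protocol article*

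**What the plan says.** Section 2.2.2 (Study design) describes one session in which every participant performs all three conditions. On allocation it says "The order of the three conditions will be randomized with control for age and gender". The legend of Fig 8 adds only that the conditions come "in randomized order across the participants". Neither place says whether the six possible sequences, or the three positions, are balanced.

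Section 2.2.3 fixes the number of runs: "they will perform two NF runs for each of the three conditions". Breaks are one minute between runs and five minutes between conditions. Section 2.2.4 keeps the data by run: "Within each run, all scores will be averaged to produce a global NF score per condition and per run".

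Section 2.2.5 makes the between-condition difference in brain activity the primary outcome. If the data are normal, "parametric repeated measures ANOVA will be used for mean comparisons"; otherwise the Friedman test is used. No period, order or run term is named. Section 2.2.1 gives the size ("Thirty healthy adults will be recruited") and section 2.2.5 the level ("A significance level of p < 0.05 will be used for all analyses"). No effect size, SD or power figure is given.

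The Discussion says of the design: "This block design, coupled with real-time feedback and repeated training, creates the conditions for neural adaptation and learning".

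**The concern.** In a crossover, a participant's age and gender are the same under all three conditions. Their main effects drop out of the condition contrast, so they are not what threatens it. What does change within a person is position: first, second or third in the session.

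The article gives reasons to expect a position effect. Instructions are deliberately implicit so that participants work out their own strategy over six runs. Sleepiness is rated before the experiment and after each condition. Calibration is done once, at the start. The Discussion links repeated training with learning.

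If the analysis compares conditions without period, any common trend over the session stays in the residual. The condition contrast is then measured less precisely, or tested against an error term that is too large. With 30 participants and no power calculation in the article, there is no stated margin to absorb that.

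**Working it through.** There is no design figure to reproduce, because the article gives no power, effect size or SD. The check therefore asks how much a session trend costs under stated assumptions.

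**Inputs from the article.** 30 participants; 3 conditions, hence 3! = 6 orders; 30/6 = 5 participants per order, so exact balance is feasible; level 0.05.

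**Assumptions.** One value per person and condition; within-person residual SD of 1; one condition differs from the other two by 0.7 SD; a linear trend of d SD per period, with d = 0, 0.25, 0.5 and 1.0.

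**Orders drawn by simple randomization, no period term.** The position difference between two conditions is ±1 with probability 4/6 and ±2 with probability 2/6. Its variance is (4/6)×1 + (2/6)×4 = 2. The variance of a paired difference rises from 2 to 2 + 2d², a factor of 1 + d². The SD of the mean contrast is √[(2 + 2d²)/30]:
- d = 0: √(2/30) = 0.26
- d = 0.5: √(2.5/30) = 0.29
- d = 1: √(4/30) = 0.37

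**Orders exactly balanced (5 each), no period term.** The contrast itself is unaffected, because each condition falls equally often in each position. The trend still sits in the residual. The centred positions −d, 0, d contribute 2d² per person, or 60d² in total, on 60 − 2 = 58 error degrees of freedom. The expected error mean square is 1 + 60d²/58: 1.26 at d = 0.5 and 2.03 at d = 1, where 1 is correct. The F test is therefore conservative.

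**Simulation** (4000 replicates per cell, within-person F test for condition). Entries are power, with type I error in brackets, in percent:

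| d | Balanced, no period | Balanced, with period | Simple, no period | Simple, with period |
|---|---|---|---|---|
| 0 | 78.2 (5.5) | 78.9 (5.1) | 80.3 (4.5) | 77.6 (5.0) |
| 0.25 | 75.5 (3.8) | 78.6 (4.9) | 75.7 (5.0) | 76.6 (4.8) |
| 0.5 | 68.4 (2.4) | 78.8 (5.2) | 69.4 (5.2) | 77.8 (5.4) |
| 1.0 | 38.2 (0.2) | 78.6 (5.3) | 46.6 (5.1) | 77.4 (5.5) |

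The mean estimate of the 0.7 effect was between 0.695 and 0.708 in every cell, so there is no systematic bias. Simulated contrast SDs under simple randomization without a period term were 0.261, 0.289 and 0.362 at d = 0, 0.5 and 1.0, in line with the formula.

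**Run.** Every condition has one first run and one second run, so an additive run effect cancels from the condition contrast.

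**The case against.** The strongest reply has four parts.

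**The text does not say that period is unbalanced.** A reader might infer that period and run are unbalanced. The document does not support this. Run is balanced by construction. Randomizing order balances period in expectation, and a scheme constrained on age and gender may also balance sequences. This stands: all that can be said is that no such balance is stated. It does not remove the point, since even exactly balanced orders lose power and become conservative without a period term.

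**Model terms may sit in an analysis plan that is not shown.** The article names repeated measures ANOVA without listing factors, so a fuller ANOVA is possible. This stands in part. The Friedman fallback, however, is a named test that ranks conditions within a person and has no place for period. On that route the article itself rules out adjustment.

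**Controlling order for age and gender is not an error.** Correct. It is harmless, and it could help if fatigue or learning differs by age. It simply does not address position.

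**The drift sizes are assumptions, and the article has mitigations.** Nothing in the article supports a drift of 1 SD per period, which exceeds the assumed effect. The Discussion sentence on learning explains the choice of a block design and does not forecast a trend within this session. Breaks and a cable support arm help. Re-baselining each score to the preceding rest period deals with signal drift, but not with learning or fatigue in the task response. At 0.25 SD per period the loss is small.

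**Conclusion.** The point holds as one of efficiency. The only control named on order concerns variables whose main effects cancel within a person. The named tests carry no stated period term, and one of them cannot carry any. A session trend then inflates the error.

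The size depends on a drift that the article does not give. Compared with the same allocation analysed with period, the power loss is at most about 3 points at 0.25 SD per period, about 8 to 10 at 0.5, and about 31 to 40 at 1.0. All of these assume a 0.7 SD effect and a linear trend.

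A reader might go further and conclude that the condition comparison is biased or its type I error inflated. The calculations do not support that. Estimates stay centred on the true effect, and type I error is about 5% under simple randomization and below 5% under balanced orders when a trend is present. A chance imbalance in order can shift the estimate in a single trial, but that is random error which the test already allows for.

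**What to change.** 1. Make the primary analysis a linear mixed model with condition, period (1–3) and run (1–2) as fixed effects and participant as a random effect. If both run values per condition enter the model, add a random term for participant within period, so that two runs of one condition are not counted as independent. If the two runs are averaged, run drops out.
2. For non-normal data, replace plain Friedman by a transformation, or by a permutation or rank-based version that keeps period.
3. For any orders not yet allocated, use the six sequences equally, 5 participants each. The age and gender control can remain.

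The cost is about 3 degrees of freedom (2 for period, 1 for run) and the loss of the simple Friedman fallback. The data are already to be kept by condition and run, so only each participant's allocated order has to be attached. Section 2.2 has acquisition ending in June 2025, so the allocation step may no longer apply; the change of model does not depend on it.

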**Fig 7 pone.0331177.g007:**
[figure not shown]
Flow chart of the study design. After checking the inclusion criteria, participants will undergo three randomized conditions of NF (EEG-based, fNIRS-based, EEG-fNIRS-based), with two runs for each condition.

#### 2.2.3. *Data acquisition procedure.*

**Preparation.** Participants will first receive an oral explanation of the objectives of the study and their individual characteristics will be assessed (i.e., MI abilities, sleepiness level, hours and quality of sleep, experience with MI or NF and regular engagement in physical or artistic activities involving the upper limbs; see the “Data and Outcomes” section for more details). Next, participants will be equipped with our EEG-fNIRS system. The participant is comfortably sitting in a chair (with upholstery), in a calm room and positioned in front of a table, facing a 27-inch screen placed approximately 80 cm from their heads. The NF tasks are performed in the dark, but, between all runs, the light is turned on. Finally, to ensure participant comfort, between each run, they have the possibility to move a bit on the chair and to drink a glass of water. They will be instructed to place their feet flat on the floor and rest their hands on their thighs to minimize unintentional hand movements during the MI task. Throughout the session, participants will be asked to remain as immobile as possible, with a particular emphasis on limiting head movements. To ensure the quality of the real-time signal, we will use the calibration option in NIRStar software (version 15.3, NIRx) and adjust the sensors until most channels meet the acceptable tolerance (i.e., no more than 10% of bad channels). We will then start the fNIRS recording to visually check for the presence of the cardiac pulse in the ΔHbO_2_ signal. Afterward, the EEG channels will be filled with gel (Super Visc, Brain Vision Solutions) and the impedance of the channels will be measured using the BrainVision Recorder software (version 1.26, Brain Products GmbH). Finally, the real-time EEG signal will be visually checked to confirm the presence of eye artifacts on the prefrontal electrodes and muscle artifacts from jaw clenching.

**Instructions and task.** Participants will be instructed that, during the NF runs, they will see a ball moving along a one-dimensional vertical gauge. They will be asked to raise and maintain the ball as high as possible by imagining movements of their left hand. To encourage self-learning, only implicit instructions will be provided, allowing participants to explore and develop their own strategies [62]. These instructions will be displayed in written form on the screen at the beginning of each NF run (instructions available on the git repository). More specifically, participants will be instructed to perform both kinesthetic and visual MI of their left hand to control the ball [63]. Engaging the non-dominant hand in right-handed individuals may require more focused attention, thereby increasing cognitive load and promoting neural plasticity [64]. Kinesthetic MI involves attempting to feel the motion while visual MI involves imagining the movement as vividly as possible [65]. The experimental protocol will consist of two phases. First, participants will complete a preliminary MI run without NF (MI-pre) to calibrate the NF scores. Second, they will perform two NF runs for each of the three conditions: EEG-based, fNIRS-based, and EEG-fNIRS-based NF. A one-minute break will be given between the two runs and a five-minute break will be provided between conditions. During the five-minute break, participants will fill out a questionnaire on the experimental computer. Each of the six NF runs will follow a block design alternating between ten 15 s rest periods and ten 15 s task periods, resulting in a 5 minutes run. The calibration session will alternate between five blocks, resulting in a 2.5 minutes lasting run. During rest periods, the screen will display a white cross and participants will be asked to focus on the cross and disengage from the MI task, allowing their thoughts to drift (see Fig 8).

